#### Observer-administered rating scales

Past-week severity of depressive symptoms is rated with the Montgomery-Åsberg Depression Rating scale (MADRS) ([47], German version: [48]). In order to ensure interrater reliability, raters use a structured interview guide ([49], own translation into German) for gathering the information needed for coding the MADRS.

The Panic and Agoraphobia Scale (PAS) by Bandelow [50] is administered to collect information on past-week occurrence of panic attacks, agoraphobic avoidance, anticipatory anxiety, disability due to panic and agoraphobia and functional avoidance. Each assessor is receiving training in the administration of the PAS scale.

In order to continuously ensure the quality of data from observer-based ratings, raters undergo regular training sessions and are supervised by a staff psychologist. Before being allowed to conduct the first interview by themselves, trainees are required to observe an experienced rater administering the interview and to conduct an interview with an experienced rater sitting in the session. In both situations, their coded sum score needs to fall within 2 points of the total score of the experienced rater. The training is continued until the criterion is met. Questions and difficulties arising from the application of the instruments are addressed in weekly meetings or immediately by contacting the supervisor. Deviations from the rating protocol are checked in regular interrater reliability meetings and booster training sessions.

#### Questionnaires

Socioeconomic status (SES): Education, occupation, current employment status, household composition/income and social class status of participants and their spouses is assessed with a questionnaire that we developed on the basis of the recommendations by the German Statistical Federal Office [51]. It includes a section for the assessment of the SES of the participant’s family of origin to determine the SES during the forming years of childhood and youth. The questionnaire additionally includes the German version of the Quality of Marriage Index (QMI-D) ([52], original version: [53]) and allows for the determination of a social prestige/status index according to international standards [54].The following depression- and anxiety-related symptom measures are used for a deeper dimensional characterization of participants:Beck-Depression-Inventory (BDI-II [55], German version: [56]) for the measurement of depressive symptom severity within the past 2 weeks.The State-Trait-Anxiety Inventory (STAI [57], German version: [58]) with the sum score of the state anxiety scale (A-State, form X1) representing an intensity measure of a transient emotional state characterized by tension, uneasiness, nervousness, fear of future events and arousal of the autonomic nervous system and the sum score of trait anxiety (A-Trait, form X2) indicating a general anxiety predisposition that is stable over time.The Body Sensations Questionnaire (BSQ) and the Agoraphobic Cognitions Questionnaire (ACQ) developed by Chambless et al. [59] for the assessment of the fear of fear (German version: [60]). The ACQ comprises three subscales: agoraphobic cognitions, loss of control and physical concerns.The Intolerance-of-Uncertainty Scale (IUS) ([61], German version: [62]) assesses reactions to ambiguous situations, uncertainty and future events and is listed in the RDoC matrix as a self-report measure for potential threat.Personality measures: The Tridimensional Personality Questionnaire (TPQ) ([63], German version: [64]) assessing novelty seeking, harm avoidance, reward dependence.

The Behavioral Inhibition and Behavioral Approach System (BIS/BAS) scales to assess approach motivation and individual differences in the sensitivity to reward and punishment ([65], original version: [66]). The newest version of the RDoC matrix lists BIS also as self-report measure for the RDoC domain potential threat.

A four-item questionnaire (IE-4) is used to measure locus of control (LOC) [67], the personal belief about whether life is controllable by own actions (internal LOC) or by external factors outside one’s influence (external LOC). LOC is assessed because it might have a strong influence on reward learning and valuation.

For a categorical and dimensional self-assessment of DSM-IV personality disorders, we use the “Assessment of DSM-IV Personality Disorders” (ADP-IV) by Schotte et al. ([68], German version: [69]). The ADP-IV specifically asks for personality features that cause stress, problems and social conflicts.

(d) Aspects of social processes are measured with the following questionnaires:

The Relationship Scales Questionnaire (RSQ) ([70], German version: [71]) was chosen for the assessment of attachment style because it operationalizes several theoretical concepts of attachment theory and it can be completed by singles. The RSQ allows for the dimensional assessment of four attachment prototypes (secure, preoccupied, dismissing-avoidant, fearful-avoidant) according to the four-category model of Bartholomew and Horowitz [72]. The RSQ comprises the 18 items of the Adult Attachment Scale (AAS [73]) from which the three subscales closeness, dependency and anxiety in relationships can be derived. The RSQ can also be scored in regard to the two dimensions attachment-related avoidance and attachment-related anxiety [74, 75].

Interpersonal pleasure is measured with the German Translation of the Anticipatory and Consummatory Interpersonal Pleasure Scale (ACIPS) [Skala der erwarteten und vollendeten zwischenmenschlichen Freude, translated by K. Kirst, University of Wisconsin-Madison] [76]. Four factors (general social interactions, close relationships, shared interests and experiences as well as family-related interactions) can be derived from the ACIPS [77].

The size of the social network is estimated with the Social Network Questionnaire (SNQ) [78] that has been derived from the social contact circle interview [79]. The SNQ asks participants to list the names of all individuals (household members, family members, friends, colleagues, neighbors, others) with whom they were in contact within the past 4 weeks.

Empathy Quotient (EQ) and Autism Quotient (AQ) are measured with the questionnaires originally developed by Baron-Cohen et al. (EQ: [80], German translation: [81], AQ: [82], German translation: [83]).
(e)Exposure to trauma, critical life events and coping strategies: The German version of the childhood trauma questionnaire (CTQ) [84] by Wingenfeld et al. [85] is used to assess sexual, physical and emotional abuse as well as physical and emotional neglect experiences during childhood. The CTQ is listed as a self-report measure for the RDoC domain “sustained threat” [86]. For collecting more detailed information on traumatization during childhood and adolescence (up to age 18) in terms of exposure frequency during certain age periods and past/current impact of the event, we additionally administer the short inventory for the assessment of early traumatic life events (K-IFTL). The K-IFTL is a modified version of the Early Trauma Inventory (ETI [87], German version: [88]) and covers the domains physical punishment/assaults, unwanted sexual experiences and general traumas (e.g., death of a close friend). We additionally added a section on emotional traumas to the K-IFTL, as emotional traumas are the most frequent childhood traumas in our patient population. Lifetime exposure to accidents, natural disasters, criminal acts, physical assaults and sexual traumas together with information on age at traumatization and exposure duration is assessed within the post-traumatic stress disorder (PTSD) section of the DIA-X/M-CIDI [41, 42]. The trauma list N1 was modified to include occurrence frequency, duration age at exposure for each trauma category. Information on current (past 6 months) exposure to negative life events is collected with a modified version of the Munich event list (MEL by [89], described in detail in [90]). Since the RDoC domain “loss” was not completely covered by our environmental measures but is of importance for the development of depressive and anxiety disorders, we developed a questionnaire for assessing experiences of loss over lifetime. This self-developed loss event questionnaire (LEQ) assesses the frequency, past/current impact and age at occurrence of several loss events such as death of parents, close attachment figures, siblings, spouses, children, close friends, separation/divorce of parents, separation/divorce from spouse/partner as well as severe (life-threatening) illnesses of loved ones.

The following stress coping strategies are assessed with a validated German stress coping inventory (Stressverarbeitungsfragebogen-78 item version, SVF78, [91]): Play down, guilt denial, substitutional satisfaction, situation control, reaction control, positive self-instruction, need for social support, active avoidance, flight tendency, rumination, resignation, self-accusation. The SVF78 additionally allows for the differentiation between stress-reducing (positive) and stress-augmenting (negative) strategies. For the measurement of psychosocial stress-resistance we used the 11 item version of the resilience scale (RS-11) ([92], German version: [93]). The RS-11 is a one-dimensional scale that conceptualizes resilience as a protective personality factor.

#### Data acquisition

Each questionnaire (except for the loss event and the SES questionnaire) was computerized and collected with an online survey tool (collector 2015.Q2 by survalyzer). The battery of questionnaires is split into three packages to reduce the load associated with filling in the questionnaires. For each package, participants receive a separate online link after the screening visit.

#### Repeated measurements

In MPIP patients, the MADRS, BDI-II, PAS and STAI-X1 are repeatedly assessed at each in-house study visit (days 14, 28 and 56) to assess the course of symptoms over time.

#### Data management

A biomedical research portal (software CentraXX by Kairos, Germany) will be used for the secure storage and management of data. The software includes a biobanking and a clinical trial management system supporting a quality-assured execution of the study. Data are entered in eCRFs (electronic case report forms) with automatic checks whether values fall within the valid range. Incomplete eCRFs are flagged. Every eCRF is checked by a second data entry assistant in regard to transferring errors and inconsistencies. Only complete and quality controlled data (flagged green) are released.

Data confidentiality and security are enforced through several mechanisms. Access to the database is password secured and restricted by role-based rights. The visibility of confidential data and the type of activity an individual user is allowed to undertake is regulated by his/her role in the study and privileges associated with the personal login data. The security architecture of the research portal implements German data protection laws.

The principal investigator ([name]) and coordinators of the study ([name]) have full access to the dataset. Access to the data for research purposes is granted by the PI upon request. Topics for publication need to be approved by the PI and communicated with the coordination team who oversee authorship regulations. Study participants, who signed that they want to be informed about publications arising from the study, receive an email notification when a publication appears. For data protection reasons, the full data set including omics data cannot be made publicly available. Access to data of published results will be granted upon request.

### Statistical analysis

The overall aim of the study is to integrate multi-level information across all assessment domains and to yield biology-based subclasses of mental disorders by using cluster analytical techniques. Previous attempts to identify biomarkers and biotypes of mental disorders have failed to identify reproducible biomarkers. So far, these studies have included fewer assessment domains, such as only neuroimaging, neurotransmitter measurements or self-report data (see e.g. [94–96]). Given the complexity of mental disorders that associate with domains like personality, life history as well as environmental, behavioral, neurobiological, and genetic factors, it is reasonable to assume that heterogeneity in mental disorders can be best understood by considering as wide a range of modalities and data sources as possible. The comparative utility of different data modalities has been examined in studies seeking to predict disease outcomes (e.g. [97]), but has not been adequately addressed with regard to more general biomarker discovery for mental disorders. To ensure that the rich data collected in this study will be used in the most beneficial way, the core analyses of this study will be planned and carried out in alignment with expert recommendations regarding development of biomarkers for psychiatric disorders [98, 99].

Two of the primary concerns that need to be addressed in our analysis approach are the integration of information from multiple data sources and the ratio of observations to possible variables to be examined. To this end, the core assessment domains - omics, neuroimaging, psychophysiology, neuropsychology, and self-report measures – will first be analyzed separately to reduce the dimensionality of the feature space. These partial analyses will include feature extraction (e.g. PCA) and feature selection steps that will inform the input into a multi-modal unsupervised learning analysis. For example, data-driven approaches will be combined with expert-based feature selection (e.g. evidence from the literature, meta-analyses) in order to include domain knowledge in the selection process. The goal of these dimensionality reduction steps is to reduce the number of input variables from multiple assessment domains to a small set of validated and generalizable features. These reduced feature set will be used as input into an unsupervised learning pipeline incorporating subsampling and cross-validation steps to guard against overfitting. An appropriate clustering approach will then be chosen based on the outcome from the previous data integration steps. Depending on the dimensionality of the final feature set, ensemble learning will be considered as a possibility for separating the contribution of the different assessment domains. This may be particularly beneficial when considering that previous research has shown domains such as self-report questionnaire assessments to account for a much larger portion of variance than omics or neuroimaging data in explaining behavioral or disease phenotypes (e.g. in alcohol use: [97, 100, 101]). By constructing separate models for different data domains, a “drowning out” of weaker effects that nevertheless contribute unique variance to a model may be counteracted.

While the prior reduction of the feature space is an important step in reducing the risk of overfitting, the suitability of our sample size for recovering existing effects is nevertheless of concern [102]. Thus far, no results from comparable studies examining affective or anxiety disorders have been reported, making it difficult to estimate possible effect sizes and determine case numbers accordingly. Therefore the determination of the case number was guided by studies with a comparable research agenda (e.g. B-SNIP study [103]). We plan to include at least 1000 patients or individuals affected by a mental disorder and 500 individuals without a mental disorder according to the DIA-X/M-CIDI. These sample sizes are comparable to the case numbers Clementz et al. used for the identification of psychosis biotypes [104] and are also informed by examinations of the changes in retrievable effects in prediction studies with low signal-to-noise data and varying sample and feature set sizes [105]. The feature reduction steps are used to keep the feature-to-observation ratio in a balance. Since the partial analyses and other projects resulting from data collected in this study will precede our main analysis, we will track the participants included in each prior examination of the data and use this information to partition the dataset into a training set including all participants previously examined and a test set including only those participants untouched in prior analyses. Consequently, any models developed based on data collected in this study will be tested on a held-over sample to avoid overfitting due to in-sample model validation [106].

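### The safeguards named for the clustering address overfitting only, so the plan could report subclasses where there is only a continuum; a one-class comparison should be fixed in advance

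*Protocol article*

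**What the plan says.** All the relevant text is in the Protocol article, Statistical analysis.

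- **Aim:** to combine information across all assessment domains and "to yield biology-based subclasses of mental disorders by using cluster analytical techniques".
- **Feature reduction:** each domain is first analysed separately. "These partial analyses will include feature extraction (e.g. PCA) and feature selection steps".
- **Clustering:** the reduced features enter an "unsupervised learning pipeline incorporating subsampling and cross-validation steps to guard against overfitting". The method is left open: "An appropriate clustering approach will then be chosen based on the outcome from the previous data integration steps".
- **Validation:** the data are divided into a training set of participants already examined and "a test set including only those participants untouched in prior analyses". Any model developed "will be tested on a held-over sample to avoid overfitting due to in-sample model validation".
- **Size:** "We plan to include at least 1000 patients or individuals affected by a mental disorder and 500 individuals without a mental disorder". This rests on comparable studies, not on a formula.

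The section gives no criterion for passing the held-over test. It names no comparison with a single group and no dimensional result as a possible outcome. Elsewhere, the overview of the Methods calls the study observational and exploratory. The Discussion section on self-report measures plans to contrast new subtypes with traditional diagnoses. The Summary and outlook describes patients falling into different disorder classes that could inform treatment selection.

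**The concern.** Overfitting and cutting a continuum into groups are different errors. An overfitted solution fails in new participants. A cut through the middle of one continuous distribution may not fail, because new participants from that distribution have the same main axis and are cut in nearly the same place. The safeguards named are all aimed at the first error. Contrasting subtypes with existing diagnoses does not test for the second error either, since a severity split would also relate to diagnosis.

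What is at stake is the main claim of the study. A low-versus-high cut along a common severity axis could pass every check that the article names and then be presented as a biology-based class.

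**Working it through.** **Inputs from the article.** At least 1000 affected participants; five core domains, reduced separately; PCA as the example of extraction; a held-over test set of unstated size. There is no alpha, power, effect size or replication threshold, so there is no stated figure to reproduce.

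**Assumptions.** 1000 participants in all, split 693/307, 307/693, 500/500 or 800/200. The figure 307 is the current sample given under Recruitment, and 1000 − 307 = 693. There are 5, 10 or 20 features, k-means is used with k = 2, 3 or 4, and each cell has 40 runs.

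**Model with no classes.** Feature j of person i is x_ij = √ρ·f_i + √(1−ρ)·e_ij, with all terms standard normal, so ρ is the shared variance. The leading eigenvalue of the correlation matrix is 1 + (p−1)ρ and the others are 1 − ρ. For p = 10 and ρ = 0.3 these are 1 + 9 × 0.3 = 3.7 and 0.7, which gives a clear main axis to cut. For ρ = 0, or after joint whitening, all eigenvalues equal 1 and no direction is preferred.

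**Agreement measures.** The test set is labelled from the training centroids and also clustered on its own. ARI = (RI − E[RI]) / (max RI − E[RI]), where RI is the Rand index; 0 is chance and 1 is identity. Prediction strength (PS) is the smallest share, over test clusters, of within-cluster pairs that the training centroids also put together. A value of 0.8 was taken as a pass.

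**Results with no classes** (ranges over splits and feature numbers):

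| ρ | k = 2: ARI | k = 3: ARI | k = 4: ARI |
|---|---|---|---|
| 0.3 to 0.5 | 0.80 to 0.90 | 0.49 to 0.80 | 0.39 to 0.72 |
| 0.1 | 0.56 to 0.77 | 0.27 to 0.37 | 0.21 to 0.27 |
| 0 | 0.02 to 0.12 | 0.04 to 0.18 | 0.04 to 0.20 |

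At ρ = 0.3 to 0.5 the PS pass was met in 62 to 93% of runs for k = 2, 0 to 57% for k = 3 and 0 to 20% for k = 4. A separate run with 15 features, a 750/250 split and ρ = 0.2, 0.3 and 0.5 gave ARI 0.84 for k = 2 at each ρ. With ρ = 0.3, 10 features and joint whitening, k = 2 gave 0.07.

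**Closer to the article's pipeline.** Each domain is reduced separately and the outputs are then combined, so correlation between domains survives. The assumed settings were five domains with three components each, a 693/307 split, k = 2, no classes and 30 runs:

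| Correlation of domain factors | ARI, unscaled | ARI, whitened within domain |
|---|---|---|
| 0.49 | 0.85 | 0.78 |
| 0.25 | 0.79 | 0.65 |
| 0.09 | 0.49 | 0.27 |

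For k = 3 or 4 the values in these runs were 0.11 to 0.72.

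**Does a one-class comparison help?** Here n = 1000, k = 2 and there were 20 runs per setting. Two checks were used: Gaussian-mixture BIC over k = 1 to 3, and the silhouette against 19 draws from a single Gaussian. The silhouette check rejects when the observed value exceeds all 19, since (0 + 1)/(19 + 1) = 0.05.

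| Truth | Hold-out ARI | BIC chose one group | Silhouette rejected one group |
|---|---|---|---|
| No classes (three settings, ρ 0.3 or 0.5) | 0.85 to 0.88 | 100% | 0 to 5% |
| Two classes 4 or 5 SD apart on one of 10 features, ρ 0.3 | 0.94 to 0.98 | 0% | 100% |

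Hold-out agreement was high in both cases. The one-class comparison told them apart.

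**The case against.** The other side has four points of substance.

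1. A reader might infer that the article offers the held-over test as proof that classes exist. It does not. The stated purpose is to avoid in-sample validation, and no pass rule is given. The agreement index and the 0.8 threshold used above are assumptions of this check.
2. A reader might infer that the plan would report subclasses whatever the data show. That does not follow. The clustering method is open, and k-means is never named. A mixture model with an information criterion can return one class, as BIC did in every classless run.
3. A reader might infer that an arbitrary split always replicates. It does not. ARI ran from 0.02 to 0.90 depending on correlation, scaling and k. The article also considers separate models per domain, which may weaken a dominant common axis.
4. The rule for the number of classes and the replication threshold may stand in a fuller analysis plan, the study is exploratory, and a new taxonomy is called a long-term aim. The Background's remark on partly arbitrary thresholds concerns diagnostic symptom counts. It does not say that the underlying biology is one continuum.

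All four stand and limit the strength of the claim. They do not remove it. The point does not rest on a missing detail. It rests on validation logic that the article does state, which covers one error and leaves open another that bears directly on the main claim.

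**Conclusion.** The concern holds in a conditional form. With a moderate common dimension and two groups, a classless continuum can replicate almost as well as real classes, so agreement in the held-over sample cannot by itself support a claim of discrete subclasses. The risk is smaller for three or four groups and slight when the features have no common axis. The correlation of the reduced features, the split, the scaling and the number of groups are not in the article, so the sizes above illustrate and do not forecast. The two-class settings were well separated; how well a one-class comparison detects weaker classes was not examined. The point deserves a change before the main analysis. It does not invalidate the data collection.

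**What to change.** Before the main analysis, write in a one-class comparison and allow one class as a result. Two ways would serve:

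- Run the identical pipeline on data simulated from a single Gaussian or copula with the covariance of the reduced features. A copula that keeps the observed marginal distributions is safer where features are skewed, because departure from a Gaussian is not in itself evidence of classes.
- Use a model-based criterion that includes k = 1.

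Claim discrete subclasses only if the observed separation exceeds that reference and the solution also replicates in the held-over sample. Otherwise report dimensions. The index and threshold are for the analysts to choose, but both should be fixed before the held-over data are opened.

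The cost is a few sentences of plan text, extra computing and the possibility of having to report no discrete classes. No new data are needed, and recruitment was still under way when the article was submitted.
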